## 566 Data analysis plan

567 The data analysis plan will be defined based mainly in two analyses: i) the per-protocol  
568 analysis, and ii) the intention-to-treat analysis (ITT). For reporting the main findings,  
569 we will use the per-protocol principle which includes children with overweight or  
570 obesity that completed pre and post intervention assessments, and attend at least 50% of  
571 the family-based lifestyle program (no minimum required for exercise program). We  
572 will focus on per-protocol principle because we are interested in knowing the “real”  
573 efficacy rather than effectiveness of our intervention. In addition to the per-protocol  
574 principle, we will also analyse the data using the ITT. Under this principle, we will use  
575 multiple imputation for observations lost at post intervention.

576 The baseline characteristics of the subjects’ in the two intervention groups will be  
577 compared using either the Student t test (for continuous variables) or the  $\chi^2$  test (for  
578 categorical variables). Differences between the intervention groups in terms of  
579 postintervention values for the primary and secondary outcomes will be also examined  
580 using the Student t test. Within group differences (pre vs. post values) in primary and  
581 secondary outcomes will be examined using the Student paired t test  
582 following per protocol and intention-to treat principles. In both the per protocol and the  
583 intention-to-treat analyses, differences between the control and exercise groups in terms  
584 of changes in primary and secondary outcomes will be examined by ANCOVA  
585 adjusting for baseline values. Cohen’s d will be used to estimate the effect size and 95%  
586 CI.

587 Significance will be set at  $P < 0.05$ . All calculations will be made using the Statistical  
588 Package for Social Sciences version 24.0 for Windows (SPSS Inc. Chicago, IL). We  
589 will also use R software (v.3.1.2) for analysis and figures.

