## 128 Objectives

129 The primary objective of the EFIGRO study is to investigate the additional effect of  
130 aerobic and strength training on hepatic fat fraction in overweight and obese children  
131 participating in a 22 weeks family-based healthy lifestyle education and  
132 psychoeducation program.

133 Secondary objectives of the study are (i) to examine the additional effect of aerobic and  
134 strength training on cardiometabolic risk in overweight and obese children participating  
135 in a 22 weeks family-based healthy lifestyle education and psychoeducation program  
136 and (ii) to evaluate the additional effect of the exercise intervention in self-esteem and  
137 well-being of overweight and obese children.

138

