## 225 Rationale and design of the healthy lifestyle education and psychoeducation 226 interventions

227 *Rationale:* Obesity is associated with many physical and psychological consequences.

228 A family-based, lifestyle intervention with a behavioural program aimed at changing  
229 dietary habits, physical activity levels and sedentary patterns provide significant  
230 decrease of overweight in children as compared to the standard care in the short and in  
231 the long-term (16, 33). Moreover, family-based lifestyle interventions can improve  
232 psychological well-being in overweight and obese children (19, 34). Therefore, the  
233 EFIGRO study will include a family-based healthy lifestyle education program  
234 conducted by experienced nutritionists.

235 Psychological factors are important determinants for behaviour changes in the treatment  
236 of obesity in children (33). Moreover, the concept of eating as a means of coping with  
237 stressors/negative emotions, i.e., emotional eating, is a mechanism by which emotion  
238 regulation relates to obesity (35). Depression, low self-esteem and bullying are much  
239 more frequent in overweight and obese children than in their non-overweight peers (17,  
240 36). Therefore, the intervention will include a family-based psychoeducation program  
241 leaded and conducted by an experienced psychologist in behaviour changes.

242 *Design:* The control and the exercise group will attend both the healthy lifestyle  
243 education and psychological education programs. Sessions will be delivered to both  
244 parents (or caregivers) and children, separately. Being aware that the intervention  
245 program demands time to the families and that this could affect the adherence to the  
246 intervention, the healthy lifestyle education and psychoeducation interventions will be  
247 developed simultaneously. Likewise, families will come to the facilities (rooms) of the  
248 Faculty of Physical Activity and Sport Sciences of the University of the Basque Country  
249 11 times for 90 minutes, once every two weeks, over the intervention. Children will  
250 attend first the healthy lifestyle education program (45 minutes/session), while their  
251 parents or caregivers are participating in the psychoeducation program (45

minutes/session), and after children will participate in the psychoeducation program, while their parents or caregivers are attending the healthy lifestyle education program.

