#### 297 **Participant retention and addressing compliance and adherence**

298 New activities on a regular basis will be introduced to maintain interest in the exercise  
299 sessions. Children will be invited to suggest appropriate activities. Throughout the  
300 project, the investigation team will be aware that success is primarily dependent on  
301 enjoyment by the children, because the amount and intensity of the exercise rely on the  
302 children's active participation. The staff will continuously try to give the children a  
303 positive experience and will celebrate and reward the success achieving the different  
304 goals of both the healthy lifestyle education and the exercise programs to motivate the  
305 participation and to maintain their interest over the 22 weeks. For instance, working on  
306 the target heart rate range in the exercise program or achieving the goal proposed in the  
307 healthy lifestyle education program (*i.e.*, having healthy breakfast every day, tasting a  
308 different fruit or vegetable every day, etc.) will be rewarded with a smiley emoticon.  
309 The participants will be marked as "absent" if the child does not attend the session or  
310 when he/she refuses to participate on proposed games or exercise activities. Parents will

311 receive telephone calls in case problems pursuing, the child will be dropped from the  
312 program to maintain the integrity and the adherence for the other children. The  
313 attendance of both children and parents or caregivers (as well as who is attending the  
314 session, father, mother, etc.) to the lifestyle education and psychoeducation programs  
315 will be also recorded. Regardless of adherence, participants will be encouraged to return  
316 to post-testing measurements. The adherence to the exercise, healthy lifestyle education  
317 and psychoeducation programs (percentage of attendance) will be used as cofounders in  
318 the statistical analyses.

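### The main findings come from a per-protocol set selected after randomisation on attendance at the programme both arms share, so it gives up the randomised comparison without isolating the efficacy of exercise

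*Protocol*

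**What the plan says.** The Data analysis plan names two analyses and ranks them. For the main findings, "we will use the per-protocol principle which includes children with overweight or" "obesity that completed pre and post intervention assessments, and attend at least 50% of" "the family-based lifestyle program (no minimum required for exercise program". The reason given is interest in the "efficacy rather than effectiveness of our intervention". Intention-to-treat follows as an addition: "principle, we will also analyse the data using the ITT. Under this principle, we will use" multiple imputation for missing post-intervention values. In both analyses the arms are compared by ANCOVA adjusted for baseline.

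Three other sections bear on this choice:

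- Objectives: the primary aim is the additional effect of "aerobic and strength training on hepatic fat fraction in overweight and obese children" who take part in the 22-week family programme.
- Rationale and design of the healthy lifestyle education and psychoeducation interventions: "The control and the exercise group will attend both the healthy lifestyle" education and the psychological education programmes, in 11 visits. The same section accepts that the time demanded of families could affect adherence.
- Exercise training intervention: only the exercise arm has the 90-minute sessions on three days a week.

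**The concern.** Whether a child enters the set that carries the headline result is known only after allocation. Completing the post-test and attending half the family sessions both reflect motivation and family circumstances, which may also affect hepatic fat. Once children are removed on that basis, the two groups are no longer guaranteed to be alike, and baseline-adjusted ANCOVA does not correct for unmeasured motivation.

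A per-protocol set is usually defended on the ground that it shows the effect in those who received the treatment. This one does not, because the randomised treatment is exercise and no exercise is required. The main conclusion would thus rest on a comparison that has given up randomisation without gaining the quantity it was meant to gain.

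**Working it through.** **1. The plan's own figures.** Sample size calculation gives 64 per group for d = 0.5 (visceral fat), 34 per group for d = 0.7, and 80 per group after 20% loss. A two-sided two-sample t-test at alpha 0.05 and 80% power gives 64 and 34 (the normal approximation gives 63 and 33), and 64/0.80 = 80. The figures reproduce. The 20% covers loss to follow-up only, not exclusion for low attendance.

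**2. Who is in the set.** Half of 11 sessions is 5.5, so 6 are needed.

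| Exercise-arm child with both assessments | Exercise sessions | Family sessions | In the set? |
|---|---|---|---|
| A | none | 6 of 11 (55%) | yes |
| B | all | 5 of 11 (45%) | no |

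The rule separates children by the component the arms share, not by the one being tested.

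**3. Possible bias under no true effect.** The protocol gives no retention by arm, no rate of attendance below 50% and no correlation between adherence and outcome, so these are assumptions. Let the least adherent fractions pE (exercise) and pC (control) be excluded, and let adherence correlate r with a favourable outcome in both arms. With φ the standard normal density and z_p the p-quantile:

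spurious difference (SD) = r × [φ(z_pE)/(1 − pE) − φ(z_pC)/(1 − pC)]

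Standard error = √(1/nE + 1/nC), with nE = 80(1 − pE) and nC = 80(1 − pC). Type I error = P(|Z + difference/SE| > 1.96).

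- Equal exclusion and equal r: the bracket is zero, so there is no bias. A 20,000-replicate simulation at 80% retention in both arms and r = 0.3 gave 0.001 SD and 5.2%.
- 20% against 5%: bracket = 0.350 − 0.109 = 0.241; n = 64 and 76; SE = 0.170. At r = 0.3: 0.07 SD, 7.1%. At r = 0.5: 0.12 SD, 11.0%.
- 30% against 10%: bracket = 0.497 − 0.195 = 0.302; n = 56 and 72; SE = 0.178. At r = 0.3: 0.09 SD, 8.0%. At r = 0.5: 0.15 SD, 13.5%. Simulation gave 7.8% and 14.6%.
- Equal retention of 80%, with selection related to outcome in the exercise arm only (r = 0.3): 0.10 SD, 8.9% by simulation.

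Against the planned d = 0.5, 0.07 to 0.15 SD is 14% to 30%. That d was set for visceral fat, since the protocol had none for hepatic fat.

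**4. Dilution and power.** If a share q of the exercise arm does no exercise and gains nothing, the effect is 0.5(1 − q): 0.45, 0.40 or 0.35 for q = 10%, 20% or 30%. Power at 64 per group is then 0.72, 0.62 or 0.51 (normal approximation), against 0.81 with no dilution. The per-protocol set does not avoid this, because it has no exercise minimum. If a further 5%, 10% or 20% of completers fail the 50% rule, about 61, 58 or 51 per group remain, and power at d = 0.5 is 0.79, 0.77 or 0.72.

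**5. How far exchanging the analyses helps.** Part of the exclusion is missing post-tests, which affect intention-to-treat too. Suppose 15 of the 20 points in the exercise arm and all 5 in control are loss to follow-up, and the imputation model ignores adherence. The remaining bracket is 0.274 − 0.109 = 0.166, and 0.166/0.241 = 69% of the bias stays. This is why the imputation model matters.

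**The case against.** The case for the plan has real weight. The attendance rule is the same in both arms, and with equal retention and equal selection it produces no bias. An exercise minimum would apply to one arm only and would damage comparability further, so its absence is not itself a source of bias; it counts only against the claim to efficacy. The Objectives describe children participating in the family programme, so an attendance rule partly fits the stated target. Assessors are blinded and the primary outcome is measured by MRI, which limits measurement bias, though not selection. An intention-to-treat analysis with the same ANCOVA is already planned.

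Two stronger readings are tempting and should not be drawn.

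- A reader might infer that refusing exercise removes a child from the main analysis, because the section on participant retention marks such a child absent and says parents "receive telephone calls in case problems pursuing, the child will be dropped from the" program. The text does not support that. An absence from exercise does not count against the 50% rule, and the section does not say that being dropped ends the family sessions. It encourages return for post-testing whatever the adherence. A dropped child leaves the set only by falling below 50% of the family sessions or missing the post-test.
- A reader might infer that the result estimates neither efficacy nor effectiveness. That goes too far: it approximates the effect of offering exercise among families engaged with the shared programme.

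What stands after all this is the ranking of the analyses and the mismatch between the set and its stated reason. The mismatch holds even if the bias is nil.

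**Conclusion.** The point holds in this form: the main findings rest on a set chosen on behaviour after randomisation, and that set does not isolate the exercise efficacy for which it was chosen. Unequal selection is plausible, because the exercise arm carries three further 90-minute sessions a week and the protocol itself links time demands to adherence, but it is not shown. The size, 0.07 to 0.15 SD with type I error 7% to 14%, rests wholly on the assumed exclusions (20% against 5%, 30% against 10%) and correlations (0.3 to 0.5); with equal selection it is zero. It should be read as an illustration of what the plan leaves open, not as an estimate for this trial. It matters because it governs the primary conclusion and is corrected largely by changing which analysis leads.

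**What to change.** In the Data analysis plan:

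1. Make intention-to-treat the main analysis: all randomised children by assigned group, baseline-adjusted ANCOVA, multiple imputation for missing post-test values.
2. Put recorded attendance in the imputation model, imputing by arm so that exercise attendance can be used where it exists. This is separate from adjusting the treatment comparison for attendance.
3. Keep the per-protocol analysis and label it supportive.
4. Optionally, if efficacy under exercise is wanted, add a complier-average estimate based on exercise attendance with assignment as the instrument. This is new work: it needs a definition of compliance and the assumption that assignment affects outcome only through exercise.

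Steps 1 and 3 are changes of wording, and step 2 uses data the protocol already collects. The sample size need not change on this account: 80 per group with 20% loss leaves 64 observed, which keeps about 80% power at d = 0.5. The costs are a somewhat diluted estimate and reliance on missing-at-random for children without a post-test, since the protocol encourages their return but cannot ensure it.

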## 139    **Methods**

### 140    **Study design**

141    The present study is a RCT (ClinicalTrials.gov ID: NCT02258126). All parents or  
142    guardians sign an informed written consent and all the children give their assent before  
143    being enrolled in the study. The study protocol has been approved by the Ethic  
144    Committee of Clinical Investigation of Euskadi (PI2014045). Since growing children  
145    are increasing in body size and undergoing developmental changes, a control group is  
146    necessary to detect changes due to training. Therefore, we compare relative changes  
147    between control and exercise groups. After baseline measurements, children are  
148    randomly allocated to the control or exercise group. Participants are followed for 22  
149    weeks. All families enrolled in the study participate in a lifestyle education and  
150    psychoeducation programs. The intervention is performed in waves so that each wave  
151    has from 15 to 20 participants. Follow-up examinations are performed in the same  
152    settings, with the same instruments and by the same investigators as in the baseline  
153    measurements.

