### 319 **Measurements**

320 All measurements, except potential confounders such as pubertal development and  
321 demographic factors, will be conducted at baseline and repeated after 22 weeks of  
322 intervention (Figure 1). Post-intervention measurements will be scheduled within three  
323 days following the last exercise session or last healthy lifestyle program session in the  
324 exercise and in the control group, respectively (**Table 2**).

325 **Table 2.** Overview of the measurements and methodology at baseline and post-test in  
326 the EFIGRO study

| Measure                                             | Methodology                       |
|-----------------------------------------------------|-----------------------------------|
| Primary outcome                              |                                   |
| Hepatic fat (%)                                     | Magnetic resonance imaging        |
| Secondary outcomes                           |                                   |
| Physical measures                            |                                   |
| Pubertal development (Tanner stage)                 | Physical examination              |
| Body mass (kg)                                      | Scale                             |
| Height (cm)                                         | Stadiometer                       |
| Waist circumference (cm)                            | Non-elastic tape                  |
| Systolic and diastolic blood pressure (mm Hg)       | Oscillometric monitor device      |
| Lean mass (kg)                                      | Dual X-ray absorptiometry         |
| Body fat percentage                                 | Dual X-ray absorptiometry         |
| Bone mineral density (g/cm  )           | Dual X-ray absorptiometry         |
| Abdominal adiposity (g)                             | Dual X-ray absorptiometry         |
| Truncal adiposity (g)                               | Dual X-ray absorptiometry         |
| Visceral abdominal adiposity (cm  )     | Magnetic resonance imaging        |
| Subcutaneous abdominal adiposity (cm  ) | Magnetic resonance imaging        |
| Biochemical measures                         |                                   |
| Glucose (mg/dL)                                     | Enzymatic spectrophotometry       |

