#### 514 **Potential confounders**

##### 515 *Pubertal development*

516 Pubertal development will be directly assessed according to Tanner criteria (genital  
517 development and pubic hair) by the paediatricians in the Paediatric Endocrinology Unit  
518 of the HUA.

519 *Physical activity, sedentary behaviour and dietary assessment*

520 Both the control and the exercise groups will attend the same healthy lifestyle education  
521 program. However, differences in changes in physical activity level, sedentary  
522 behaviour and dietary habits could be potential confounders on the effect of the  
523 intervention on hepatic fat and cardiometabolic risk factors.

524 Physical activity will be objectively measured by accelerometry. Children will be asked  
525 to wear an accelerometer on their non-dominant wrist (wActisleep-BT, USA) for seven  
526 consecutive days all the time, except for water-based activities. Thresholds will be used  
527 to classify raw counts per minute into intensities of physical activity (66). Information  
528 about sleep duration and quality will be also obtained from the accelerometers.

529 Participants will also complete a diary log. A self-reported sedentary behaviour  
530 questionnaire (67) will be administered to the children. Participants will report the  
531 frequency of specified sedentary behaviours using predefined response categories  
532 separately for weekdays and weekends. Behaviours to be assessed include watching TV,  
533 playing computer games, playing video games or phone games, surfing the Internet for  
534 recreation, surfing the Internet for study purposes, and studying (nonschool time).

535 Dietary intake will be evaluated by two non-consecutive 24h recalls within a period of  
536 seven days. Children will report all their food and beverage ingestions assisted by  
537 nutritionists. Moreover, dietary habits and patterns will be evaluated by two different  
538 food frequency questionnaires: the KidMed index for the children (68) and a validated  
539 food frequency questionnaire for the parents or caregivers (69). The KidMed index was

540 developed to estimate adherence to the Mediterranean dietary pattern in children and  
541 young adults, based on foods/dietary patterns that sustain it.

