#### 542 *Socio-demographic variables*

543 A parental questionnaire will be used to collect information about socioeconomic status,  
544 demographic characteristics, neonatal data of the children and family medical history of  
545 obesity, diabetes, dyslipidemia and hypertension. The Family Affluence Scale will be  
546 used as an index of socioeconomic status. The Family Affluence Scale is an indicator of  
547 affluence *versus* material deprivation and describes family expenditure and  
548 consumption based on 4 items: having an own bedroom, number of cars per family,  
549 number of PCs at home and internet access(70). The Family Affluence Scale has been  
550 widely used as an index of socioeconomic status(71, 72). Other indicators of  
551 socioeconomic status will be used: the parental education level (primary school,  
552 secondary school/technical training or university degree), and parental occupation  
553 according to the International Standard Classification of Occupation  
554 (<http://www.ilo.org/public/english/bureau/stat/isco/index.htm>). Demographic  
555 characteristics will include date of birth, sex, ethnicity and family structure. Perinatal  
556 data will include weight (g), length (cm) and head circumference at birth (cm),  
557 gestational age (weeks), and duration of both breastfeeding and exclusive breastfeeding  
558 (months).

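### The between-group ANCOVA adjusts only for baseline values and does not use sex, age or Tanner stage, although the protocol collects them and calls pubertal development and demographic factors potential confounders

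*Protocol*

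**What the plan says.** The Data analysis plan compares the arms in terms "of changes in primary and secondary outcomes will be examined by ANCOVA", "adjusting for baseline values", and applies this to the per-protocol and the intention-to-treat sets alike. No other covariate is named there. The same section adds that "postintervention values for the primary and secondary outcomes will be also examined", by an unadjusted t test. It takes the main findings from the per-protocol set: children with both assessments who attended at least half of the lifestyle program.

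Elsewhere the protocol treats maturity and demographics as relevant. Study design justifies the control group because growing children "are increasing in body size and undergoing developmental changes, a control group is" needed to isolate the training effect. Under Potential confounders, "Pubertal development will be directly assessed according to Tanner criteria". Under Socio-demographic variables, demographic "characteristics will include date of birth, sex, ethnicity and family structure". The Measurements section reads "All measurements, except potential confounders such as pubertal development and" demographic factors, and sets these apart from what is repeated after 22 weeks. The measurements overview (the second of two tables numbered 2) lists Tanner stage twice, as a secondary outcome and as a potential confounder.

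The only other general adjustment is in the section on retention and adherence, where adherence to the exercise, lifestyle "and psychoeducation programs (percentage of attendance) will be used as cofounders in" the analyses. The Randomization section describes a computer-generated allocation with no stratification factor.

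**The concern.** Variables that the protocol itself calls potential confounders, and that are fixed before allocation, are missing from the covariate set that it writes down. The one further covariate it promises for the analyses in general, attendance, arises after randomisation.

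If sex, age and maturity predict 22-week change beyond the outcome's own baseline value, leaving them out keeps explainable variation in the error term and leaves any chance imbalance in the estimate. Selection into the per-protocol set happens after randomisation, so the arms there may differ on these variables by more than chance. A long, unranked list of potential confounders with no stated use also leaves room to choose covariates once results are visible.

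**Working it through.** **1. The plan's own figure.** From Sample size calculation: d = 0.5 (visceral fat), d = 0.7 (insulin resistance, body fat), 80% power, α = 0.05 (taken as two-sided), 20% loss. The exact two-sample t calculation gives 63.77, so 64 per arm, and 33.02, so 34 per arm. Then 64/0.8 = 80 per arm, 160 in total. All the stated figures reproduce. None depends on extra covariates.

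**2. Precision and power.** Let R² be the share of residual variance, after baseline adjustment, that sex, age and Tanner stage explain. The documents give no value, so a range is assumed. Take d = 0.5 as the standardised effect after baseline adjustment, and n = 64 per arm.

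- Residual SD, and so interval width, is multiplied by √(1 − R²).
- Non-centrality = 0.5/√(1 − R²) × √(64/2).
- Residual df = 128 − 2 − k. Baseline value only: k = 1, df = 125. Adding sex (1), age (1) and Tanner stage in three groups (2): k = 5, df = 121.
- Baseline only: non-centrality 0.5 × √32 = 2.828, critical t 1.979, power 80.14%.

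| Assumed R² | Non-centrality | Power, added covariates | Interval narrower by | Equivalent extra children per arm, 64/(1 − R²) − 64 |
|---|---|---|---|---|
| 0% | 2.828 | 80.1% | 0% | 0 |
| 2% | 2.857 | 80.9% | 1.0% | 1.3 |
| 5% | 2.902 | 82.1% | 2.5% | 3.4 |
| 10% | 2.981 | 84.1% | 5.1% | 7.1 |
| 15% | 3.068 | 86.1% | 7.8% | 11.3 |

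At R² = 0 the 4 degrees of freedom alone move power from 80.14% to 80.12%.

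**3. A limit on these figures.** The table takes the arms as balanced on the added covariates. Averaged over chance imbalance, the variance of the arm effect with k covariates is inflated by about (N − 3)/(N − k − 3). With N = 128 this is 125/124 for k = 1 and 125/120 for k = 5, a ratio of 124/120 = 1.033. That is worth 64 − 64 × 120/124 = 2.1 children per arm, and the average break-even R² is 1 − 120/124 = 3.2%. Below that the covariates buy conditional accuracy but no average precision.

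**4. Chance imbalance.** At 64 per arm, 95% of allocations give a standardised covariate difference within ±1.96 × √(2/64) = ±0.35. If one covariate carried the whole R², the estimate at that limit would shift by √R² × 0.35: about 0.05, 0.08, 0.11 and 0.13 residual SD at R² of 2, 5, 10 and 15%, against an assumed effect of 0.5.

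**The case against.** The strongest objection is that this is a preference rather than a fault. The protocol fixes the model family and the covariate that usually matters most, and further prognostic covariates are often left to a statistical analysis plan, which is not shown here. Calling variables potential confounders may signal that they will be used. This stands in part, and it limits the weight of the point. But the section does not stay silent on covariates. It states a set, and that set does not match the protocol's own list.

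Three stronger readings are tempting, and the documents do not support them.

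- A reader might infer that the trial has only this one analysis. It does not: t tests are also listed, attendance is promised as an adjustment, and the fitness section says that analysis will account for whether true VO2max was reached.
- A reader might infer that the comparison is biased. In the full randomised set it is not, and its interval and p-value already allow for chance imbalance.
- A reader might infer that precision is demonstrably lost. No R² is given, the outcome's baseline value is already in the model, and eligibility (ages 9 to 11, girls before menarche) narrows age and maturity. The d = 0.5 belongs to visceral fat, so no gain is shown for hepatic fat.

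The chance of a sex imbalance should also be read with care. With an assumed 50:50 split, the probability of a between-arm difference of at least 10 percentage points is 21.6% at 64 per arm and 26.8% at 80. The apparent rise is an artefact of discreteness: the smallest reachable difference of that size is 8/64 = 12.5 points at 64 per arm, but exactly 10 points at 80.

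**Conclusion.** The point holds as a worthwhile improvement, not as a validity fault. The stated ANCOVA omits pre-randomisation variables that the trial collects and itself flags. In the intention-to-treat comparison the cost is efficiency and conditional accuracy: between nothing and about 6 power points over an assumed partial R² of 0 to 15%, at 64 per arm and d = 0.5, with no average gain below roughly 3%. In the per-protocol set, adjustment would reduce imbalance on these measured variables, but it cannot undo selection on completion and attendance.

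The conclusion assumes that Tanner stage, which is not repeated, is recorded before allocation. The double listing of Tanner stage is clerical: a variable measured once cannot be analysed as a change, though it can still describe the sample at baseline.

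**What to change.** In the Data analysis plan, before unblinding, specify the ANCOVA for the primary and all secondary outcomes, in both the per-protocol and the intention-to-treat analyses, as: arm + baseline value of the outcome + sex + age at baseline + baseline Tanner stage. Combine sparse Tanner stages by a rule set without reference to outcome data. Use baseline values only, so attendance does not belong in this model, and reconcile the adherence section with it. In the measurements overview table, list Tanner stage only as a baseline covariate.

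The cost is a sentence or two of text, about 4 degrees of freedom out of 125, and a small average loss of precision if the covariates turn out to predict almost nothing. No new data are needed.
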